### Power calculation

On the basis of experiences in the German competence network [67] and the European First Episode Schizophrenia Trial (EUFEST) study [68], we assumed a one-year discontinuation rate of 68% in the control group.

To demonstrate superiority of 20 percentage points in the one-year discontinuation rate in the intervention group by two-sided testing with an error probability of *α* = 0.05 and a power of 1 − *β* = 0.8 in the chi-square test, we have to include about *n* = 90 participants in each study arm (software used: Power and Sample Size Calculation [PS] 3.0.43, freely available at https://biostat.mc.vanderbilt.edu/PowerSampleSize). It should be noted that the expected number of missing values for the endpoint *all-cause discontinuation* is (close to) zero. In addition, the expected power of the corresponding hypothesis test (e.g., log rank test, Cox regression) is slightly greater if the respective event time is taken into account.

### Planned data analyses

The primary analysis is according to the intention-to-treat (ITT) (full analysis set) and includes all randomized participants; only (clearly ineligible) subjects randomized in error will be excluded.

To compare the distribution of the primary endpoint *all-cause discontinuation* between the two treatment groups, we use stratified (by center) Cox regression with main effects treatment (intervention vs. control group), antipsychotic therapy, participants age, and sex (no interactions) at two-sided significance level 5%. Moreover, the influence of the covariate duration of illness is explored.

To confirm the stability of the model adaptation, we will pool the data of centers with low recruitment rates (< 8 randomized participants).

We will test the assumption of proportional hazard functions by adding time-dependent covariables. In addition, we will apply methods for competing risks (such as nonadherence, insufficient efficacy, and side effects of the medication).

We will analyze changes in neurocognitive performance, psychopathological symptoms, level of functioning, quality of life, cardiovascular risk factors, metabolic parameters, and physical fitness with linear mixed models for repeated measurements (MMRM; main effects: group, center, sex, participants age, (possibly) duration of illness, time, individual antipsychotic therapy, and the interaction group × time) and generalized estimation equations (GEE), both between groups and over the course of the study. Adjustment for multiple testing will be based on the closure test principle, for example the sequentially rejective Bonferroni–Holm method [69, 70]. Depending on the distributional characteristics, we may apply non-parametric methods.

We will perform a subgroup analysis by sex, center, and individual antipsychotic therapy and will investigate the possibly moderating influence of patient characteristics, especially duration of education or severity of disease (CGI). Adverse events will be summarized and compared between study arms according to the type, relationship to study intervention, severity, and intensity. The analyzing statistician will be blinded while transforming and analyzing the data.

In a primarily explorative approach, we will analyze the gene expression, epigenetics, proteomics, and MRI data by multivariate methods (e.g., statistical parametric mapping [SPM], projection to latent structure [PLS], machine learning approaches).

A sensitivity analysis will investigate the structure of the missing values (e.g., missing completely at random [MCAR], missing at random [MAR], or not missing at random [NMAR]) and explore the influence of different strategies for handling missing values (e.g., different imputation methods). In addition, we will investigate whether there was a clustering effect due to identical therapists or centers [71].

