### Study population

The study includes in- and outpatients (men and women) aged from 18 to 65 years with a primary diagnosis of schizophrenia according to the Diagnostic and Statistical Manual of Mental Disorders 4th Edition, Text Revision (DSM-IV-TR 295.10-30, 295.90). Participants are assessed by the Mini-International Neuropsychiatric Interview [36] (M.I.N.I. Version 6.0.0). Further inclusion criteria are the ability to provide informed consent; stable psychopathology, indicated by a total Positive and Negative Syndrome Scale (PANSS) score ≤ 75 (no minimum value); and treatment with one or two antipsychotics (including clozapine) in accordance with the current treatment guidelines. The active substance and dose of the antipsychotic medication with which the patient has reached psychopathological stability must be constant for at least 2 weeks prior to inclusion in the study. The additional administration of antipsychotics as rescue medication for restlessness and sleep disorders is permitted if the daily dosage does not exceed 150 chlorpromazine equivalents. Concomitant psychotherapy and other psychosocial treatments are allowed (if administered, details are noted). Additional inclusion criteria are a negative pregnancy test (serum) at baseline and use of a reliable method of contraception in female participants and a body mass index between 18 and 40 kg/m^2^.

Exclusion criteria are an inability to give informed consent; presence of suicidality or being a risk to others; severe somatic or neurological comorbidities; history or assumption of relevant non-compliance that interferes with the ability to participate in a clinical trial; positive urine drug screening (except benzodiazepines); lack of German language skills; and pregnancy or lactation.

With regard to the recruitment process, inpatients and outpatients are screened regularly at the study sites. In a next step, an investigator informs each potential participant (as well as the legal representative, if applicable) comprehensively in verbal and written form about the objectives, procedures and possible risks of the study. A signed informed consent is obtained from each participant (and legal representative, if applicable) prior to any study-related procedure.

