### Study endpoints

The primary endpoint is *all-cause discontinuation*, defined as relevant worsening of symptoms to a total PANSS score > 75 (on consecutive visits, for more than 14 days), severe adverse effects, non-compliance with the training program or diagnostic examinations for more than 6 weeks, an inability to reach the participant, or an unwillingness of the participant to continue participating in the study despite intensive efforts by the study team. The primary endpoint is evaluated at each visit. *All-cause discontinuation* is a comprehensive outcome that can be reliably assessed and reflects the participants’ satisfaction with the intervention and its tolerability and efficacy [43].

Secondary endpoints include changes in neurocognitive performance, psychopathology, level of functioning, quality of life, cardiovascular risk factors, metabolic parameters, and physical fitness. To measure neurocognitive performance, we assess verbal declarative memory with the German version of the Rey Auditory Verbal Learning Test (Verbaler Lern- und Merkfähigkeitstest, VLMT) [44],overall cognitive impairment and attention with the Digit Symbol Substitution Test (DSST) [45] and Digit Span Test [45],and verbal fluency with the Brief Cognitive Assessment Tool for Schizophrenia (B-CATS) [46]. Furthermore, we measure processing speed with the digit–symbol coding part of the DSST, and complex visual scanning, motor speed, and the ability to shift strategies with the Trail Making Tests A and B (TMT-A/B) [47]. Finally, we evaluate social cognition with the Facial Affect Recognition Test (PFA) and the Movie for the Assessment of Social Cognition (MASC) [48].

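### The primary Cox model omits baseline PANSS total, although the entry ceiling is also the cut-off of one endpoint component; precision is probably left unused

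*Protocol article*

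**What the plan says.** Planned data analyses sets the primary model as "stratified (by center) Cox regression with main effects treatment (intervention vs. control group), antipsychotic therapy, participants age, and sex (no interactions", tested two-sided at 5%. Duration of illness is to be explored in addition. Disease severity, measured by CGI, appears only as a possible moderator outside the primary model. Baseline PANSS total is not mentioned as a covariate.

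Study population makes "stable psychopathology, indicated by a total Positive and Negative Syndrome Scale (PANSS) score" of 75 or less an entry condition and states that there is no minimum. Study endpoints lists, as the first of five ways to meet the primary endpoint, "relevant worsening of symptoms to a total PANSS score" above 75, sustained on consecutive visits for more than 14 days. The other four are severe adverse effects, non-compliance for more than 6 weeks, inability to reach the participant, and unwillingness to continue.

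In Power calculation, "we assumed a one-year discontinuation rate of 68% in the control group". The trial is sized for a difference of 20 percentage points with "a power of 1 − *β* = 0.8 in the chi-square test", giving about 90 "participants in each study arm". No credit is taken for covariates.

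**The concern.** The event threshold for the PANSS component is the entry ceiling. A participant who enters at 75 crosses it with a rise of 1 point; one who enters at 45 needs 31 points. Baseline PANSS is thus tied to one part of the primary endpoint by definition, and it is known for everyone because eligibility depends on it. The model adjusts for age, sex and antipsychotic therapy but not for this score.

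Adjusting a Cox model for a prognostic baseline covariate generally raises the power of the treatment test. It also accounts for a chance difference between arms in how many participants enter close to the threshold. At stake is precision in a trial with little to spare: 162 of 180 participants were already randomized when the article was submitted, so the sample size is largely fixed.

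**Working it through.** **1. The plan's own figure.** Inputs from Power calculation: 68% versus 48%, two-sided α = 0.05, power 0.80.

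- Unpooled variance: n = (0.68·0.32 + 0.48·0.52)·(1.960 + 0.842)² / 0.20² = 0.4672·7.85 / 0.04 ≈ 91.7, so 92 per arm.
- Pooled chi-square without continuity correction: 95 per arm, or power 0.78 at 90 per arm.

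The stated figure of about 90 is therefore approximately reproduced.

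**2. Event-time power without baseline PANSS.** Under proportional hazards, HR = ln(0.52)/ln(0.32) = 0.574. Expected events are 90·0.68 + 90·0.48 = 104.4. By Schoenfeld's formula, √(104.4/4)·|ln 0.574| − 1.96 = 5.11·0.555 − 1.96 ≈ 0.88, which gives power of about 0.81. This agrees with the article's remark that the event-time analysis has slightly more power than the chi-square test.

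**3. Power with baseline PANSS, acting on the PANSS component only.** Simulation with 90 per arm, one year of follow-up, marginal rates held at 68% and 48%, and 3,000 trials per scenario (Monte Carlo standard error about 0.007). The covariate is standard normal; center strata and the other covariates are left out. Two inputs are assumed: the share of the control hazard due to the PANSS component, and that component's hazard ratio per SD of baseline PANSS. Entries are power without → with the covariate.

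| PANSS share | HR/SD 1.5 | HR/SD 2 | HR/SD 3 |
|---|---|---|---|
| 10% | 0.819 → 0.813 | 0.796 → 0.796 | 0.790 → 0.789 |
| 20% | 0.802 → 0.805 | 0.811 → 0.818 | 0.813 → 0.819 |
| 30% | 0.805 → 0.801 | 0.818 → 0.828 | 0.799 → 0.825 |
| 50% | 0.805 → 0.812 | 0.815 → 0.838 | 0.819 → 0.877 |
| 100% (extreme bound) | 0.807 → 0.845 | 0.822 → 0.923 | 0.839 → 0.984 |

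Up to a 30% share the gain is 0 to 3 points. At 50% it is about 1 to 6 points, depending on prognostic strength.

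**4. If baseline PANSS also predicts the other components.** With a hazard ratio per SD of 2 to 3 on the PANSS component and a weak 1.2 to 1.35 on the rest (all assumed), power rises from 0.81–0.82 to 0.84–0.85 at a 20% share, from 0.80–0.81 to 0.83–0.87 at 30%, and from 0.81–0.82 to 0.86–0.90 at 50%. Across the stronger scenarios, meaning a share of about half or such a link, the gain is about 4 to 11 points.

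**5. Upper range.** If the covariate acts on the whole hazard at 1.35, 1.65 or 2.0 per SD, power goes from about 81% to 84%, 88% or 92%. The last figure matches the 100% row above (0.923 at HR/SD 2).

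**6. If baseline PANSS is not prognostic.** Power with and without it is the same within simulation error (0.799 versus 0.795; in another run 0.808 versus 0.809).

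**The case against.** The strongest reply is that nothing in the plan is wrong. The model is prespecified and valid under randomization, the sample size rests on an unadjusted test, and event-time power is about 0.81 without this term. Which prognostic covariates to add is partly a matter of preference. That stands, and it limits the point to efficiency.

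Three stronger readings are tempting, and the article supports none of them.

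- A reader might infer that power of 84% to 92% is being forgone. Those figures apply the covariate effect to every cause of discontinuation, whereas only one component of five is tied to the cut-off. The article gives neither the split of events by component nor any evidence that PANSS predicts withdrawal or loss of contact.
- A reader might infer that the unadjusted hazard ratio is biased towards 1. At 2.0 per SD on the whole hazard, 0.575 without and 0.515 with adjustment are a marginal and a conditional hazard ratio. Both are correct for what they estimate, and 0.575 fits 68% versus 48%. Chance imbalance is likewise already allowed for in the type I error; adjustment improves precision but repairs no flaw.
- A reader might infer that baseline PANSS decides the PANSS component almost mechanically. The score must stay above 75 for more than 14 days, other discontinuations intervene, and a high entry score tends to regress. Assuming no true change, a visit SD of 8 and correlation 0.5, the chance of two consecutive readings above 75 is about 11%, 32% and 62% from entry at 65, 70 and 75. It falls to about 7%, 21% and 44% once other discontinuation at the assumed 68% is allowed for, and regression to the mean lowers it further. A gradient remains, but a weaker one.

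**Conclusion.** The point holds as a missed efficiency gain. The covariate list is fixed in the article and leaves out the one baseline score built into the endpoint definition. The likely return is 0 to 3 points of power if PANSS events are at most 30% of the hazard and baseline PANSS matters only for them. It is about 4 to 11 points if they are about half, with strong prognosis, or if baseline PANSS also predicts withdrawal; at a half share with weak prognosis it is nearer 1 to 2. All of this rests on assumed component shares and prognostic strengths. Neither the validity of the primary test nor the stated sample size is called into question.

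**What to change.** Prespecify baseline PANSS total, as a continuous term, in the primary Cox model alongside antipsychotic therapy, age and sex, stratified by center, and record the change before unblinding. The score is collected at entry, so no new data are needed. The only downside is that the treatment hazard ratio becomes conditional on one more covariate, which the report should state; giving the hazard ratio without this term beside it would keep the link to the planning assumption.

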To increase the motivation of the participants, we address several aspects in both groups: One of the main incentives for people with severe mental illness to engage in exercise is improving physical health [40]. Therefore, we inform the participants that the training modalities have been adapted to that purpose. In addition, they are updated regularly about their progress regarding the training parameters. One of the most common barriers for engaging in exercise is the lack of social support [40]. However, supervised exercise in small training groups helps to establish a close relationship between participants and study staff, which contributes to maintain motivation and adherence. Overall, exercise supervision has been shown to result in significantly greater physical and psychological benefits [23]. Therefore, our intervention is conducted by qualified and trained personnel. Besides, the regular exercise appointments can be helpful to improve the participants' daily routine, which might also increase adherence.

After giving informed consent, participants complete the diagnostic, clinical, and neurocognition- and performance-related baseline assessments. Both groups undergo performance testing, which consists of a lactate threshold test on a bicycle ergometer. Participants start at 25 watts, then the wattage is increased by 25 watts every 3 min until the participant is exhausted or cardiovascular risk factors occur [according to 41]. The wattage and respective lactate values are recorded.

Both groups participate in three training sessions per week. To reduce the risk of injury and promote recovery, participants start and end each training session with a 5-min warm-up and 5-min cool-down phase at 80% of the intensity of the main training. The duration of the main part of the training sessions is increased after 6 and 12 weeks: The total duration of the sessions in weeks 1–6 is 40 min; in weeks 7–12, 45 min; and in weeks 13–26, 50 min. Trained study personnel accompany, control and document each training session in both groups by measuring heart rate and subjective exertion [according to 42] every 5–10 min and lactate concentration by random sampling every 4 weeks.

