Psychopathological measures include the PANSS to assess positive and negative symptoms [49], Functional Remission of General Schizophrenia (FROGS) scale to assess functional remission status [50],Clinical Global Impression (CGI) scale to assess disease severity [51],and Calgary Depression Scale for Schizophrenia (CDSS) to assess depressive symptoms [52]. The level of general functioning is evaluated with the Global Assessment of Functioning scale (GAF) [53],Social and Occupational Functioning Assessment Scale (SOFAS) [54],Personal and Social Performance Scale (PSP) [55], and University of California San Diego Performance-based Skills Assessment (UPSA-B) [56]. Quality of Life is assessed with the World Health Organization Quality of Life-Bref (WHOQOL-Bref) [57], and compliance, with the Drug Attitude Inventory (DAI) [58] and the Service Engagement Scale (SES) [59]. We also determine care costs, cost-effectiveness of the study intervention, and costs of quality-adjusted life years (QALYs) [60]. Furthermore, we investigate participants’ dynamic variation in symptoms, affect, stress reactivity, social context, and sleep with ecological momentary assessments [61].

Cardiovascular risk factors and metabolic parameters include heart rate, blood pressure, body mass index, waist circumference, triglyceride level, total cholesterol, high-density lipoprotein cholesterol, low-density lipoprotein cholesterol, fasting blood glucose, and hemoglobin A1c.

The assessment of physical fitness includes an ergometer-based lactate threshold test to assess endurance capacity. Additionally, we evaluate the level of physical activity with the self-report International Physical Activity Questionnaire (IPAQ) [62] and, if participants agree, with the Activ8 accelerometer as an objective measure.

Adverse events and serious adverse events are documented in accordance with the established definitions and legal requirements.

Safety measures include a physical examination, electrocardiography, and repeated laboratory assessments and measurements of blood pressure and heart rate. Before participants are enrolled in the study, we exclude pregnancy and acute drug abuse. As described above, the exercise training was designed to be tolerable even for participants inexperienced in exercise. Consequently, participation is not associated with a health risk. However, a doctor is always on call should any physical health problems occur during the training sessions.

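### The primary Cox model could gain some power by prespecifying baseline fitness, engagement and PANSS as covariates; this is an efficiency improvement, not an error

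*Protocol article*

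**What the plan says.** **Model.** The protocol article (Planned data analyses) specifies a Cox regression stratified by centre with "main effects treatment (intervention vs. control group), antipsychotic therapy, participants age, and sex (no interactions", tested at "two-sided significance level 5" per cent. Duration of illness is only explored.

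**Endpoint.** All-cause discontinuation (Study endpoints) has five components. Two are clinical: a PANSS total above 75 that persists, and severe adverse effects. The other three concern engagement: "non-compliance with the training program or diagnostic examinations for more than 6 weeks, an inability to reach the participant", and unwillingness to go on with the study. No expected split of events between components is given.

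**Baseline data.** Under Description and fidelity assessments: "Both groups undergo performance testing, which consists of a lactate threshold test on a bicycle ergometer". It is described with the baseline assessments, and wattage and lactate values are recorded. Study endpoints adds "compliance, with the Drug Attitude Inventory (DAI) [58] and the Service Engagement Scale (SES"; the text does not say at which visits these scales are taken, and the flowcharts are not reproduced in the copy reviewed. A PANSS total of 75 or less is an entry criterion (Study population).

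**Sample size.** In Power calculation, "we assumed a one-year discontinuation rate of 68% in the control group". The target is "superiority of 20 percentage points in the one-year discontinuation rate in the intervention group" at 80% power; "in the chi-square test, we have to include about" 90 participants per arm. No credit is taken for covariates.

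**The concern.** In a Cox model, leaving out a strongly prognostic baseline variable pulls the estimated treatment log hazard ratio towards zero and costs power, even under perfect randomisation. None of the three covariates in the primary model measures engagement or exercise capacity directly, although most of the listed event components concern staying engaged. The protocol itself stresses that these patients are often deconditioned.

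The planned size leaves little reserve: it reaches about 80% only if the full 20-point difference is real. Recruitment was at 162 of 180 when the article was submitted, so adjustment for baseline data already collected is one of the few ways left to gain precision. At stake is a modest amount of power. The validity of the primary test is not in question.

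**Working it through.** **1. The protocol's own figure.** Inputs from Power calculation: 68% vs 48%, two-sided α = 0.05, 90 per arm.

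- Chi-square, pooled variance: mean rate 0.58. Power = Φ[(0.20·√90 − 1.96·√(2·0.58·0.42)) / √(0.68·0.32 + 0.48·0.52)] = Φ[(1.897 − 1.368)/0.684] = Φ(0.774) = 78.1%.
- Sample size with unpooled variance: (1.96 + 0.842)² · 0.4672/0.04 = 92 per arm (rounded up).
- Event-time test: HR = ln(0.52)/ln(0.32) = 0.574 under exponential times. Expected events = 90 × (0.68 + 0.48) = 104.4. Schoenfeld power = Φ[√(104.4/4)·|ln 0.574| − 1.96] = Φ(0.877) = 81.0%.

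The figure of about 90 per arm is reproduced, and so is the statement that using event times gives slightly more power. The planned model reaches its target on its own inputs.

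**2. What adjustment would add.** The documents give no association between SES, DAI, fitness or PANSS and discontinuation, so the hazard ratio per SD of a prognostic baseline index is assumed and varied. Simulation: 4,000 trials per scenario, 90 per arm, exponential times, censoring at one year, marginal one-year rates held at 68% and 48%. A Cox model with treatment only is compared with one that adds three baseline covariates, one carrying the assumed effect and two pure noise.

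| Assumed HR per SD | Power without | Power with | Change (points) |
|---|---|---|---|
| 1.0 | 80.0% | 79.8% | −0.2 |
| 1.2 | 79.4% | 80.6% | +1.2 |
| 1.35 | 79.7% | 82.4% | +2.7 |
| 1.5 | 81.1% | 85.2% | +4.1 |
| 1.75 | 82.3% | 89.3% | +7.0 |
| 2.0 | 82.9% | 92.9% | +10.0 |

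The Monte Carlo standard error of each power is about 0.6 points or less. Under the null, with HR per SD 1.5, the type I error is 5.0% with and without adjustment.

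**3. Sensitivity.** A smaller simulation (about 540 to 600 trials per scenario) with five equal centres and a centre-stratified model gave gains of about 2, 4 and 10 points at HR per SD 1.3, 1.5 and 2.0. A further one with a single noise covariate gave about 0, 1, 2, 4 and 8 points at 1.0, 1.2, 1.3, 1.5 and 2.0, and slightly less where the prognostic covariate overlapped with age.

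**4. Room in the model.** If antipsychotic therapy is coded as one coefficient, the protocol's model has four (treatment, antipsychotic therapy, age, sex). Two more leave 104.4/6 = 17.4 events per coefficient, and three more leave 104.4/7 = 14.9.

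**The case against.** The strongest reply is that nothing here is wrong. The model is prespecified, the randomised test is valid without further covariates, and the sample size does not depend on them. That stands, and it limits the point to an improvement.

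Several tempting stronger readings are not supported:

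- *The endpoint is driven largely by non-compliance with exercise.* Counting components is not counting events, and no event shares are given. Only one component names the training, and it also covers the diagnostic examinations. Training ends at week 26 of 52.
- *Power is being given away.* This is conditional on prognostic strength, which is unknown. With weak predictors the gain is about zero.
- *Adjustment costs nothing.* Missing baseline values would drop randomised participants unless they are handled, and the hazard ratio becomes a different, conditional quantity.

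The candidate covariates also have real limits. DAI and SES concern attitude to medication and engagement with services, not exercise adherence. Relevant non-compliance is an exclusion criterion, which narrows their range; the PANSS limit at entry likewise narrows baseline PANSS. Training wattage is set individually from each participant's own test, and control exercises are not regulated by that test, so absolute fitness may predict dropout only weakly. Wattage may overlap with age and sex, which are already in the model. The main simulation omits those covariates and the centre strata, so its gains are, if anything, somewhat generous.

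Against this, being unreachable, unwilling or absent from examinations can also occur during follow-up, where service engagement is arguably the closer construct. The assumed 68% control rate leaves ample outcome variation. Even a useless covariate cost only 0.2 points in simulation, within Monte Carlo error.

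**Conclusion.** The point holds as an optional efficiency improvement. The primary model adjusts for antipsychotic therapy, age and sex only, while baseline fitness and PANSS, and probably SES and DAI, are available and plausibly closer to the endpoint. The expected power gain is about 0 to 10 percentage points: 0 to 1 at HR per SD 1.0 to 1.2, 2 to 4 at 1.3 to 1.5, and 7 to 10 only for strong predictors, near 2. No type I error cost was seen.

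This rests on assumed prognostic strengths, on the planning rates of 68% and 48%, and, for SES and DAI, on measurement at visit 1, which the text does not state. A reader might infer that the trial is underpowered or its treatment comparison biased because of the omission. The documents do not support that: the planned model reaches about 80% power on its own inputs, and the omission leaves the randomised test valid.

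**What to change.** Before unblinding, prespecify these additional continuous covariates in the primary Cox model:

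- baseline lactate-threshold wattage, derived in the same way in both groups from the recorded test values;
- baseline SES total if taken at visit 1, otherwise baseline DAI if that was taken then;
- baseline PANSS total, as a natural companion: it is known for every eligible participant from the entry criterion and tied to the PANSS component of the endpoint.

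Impute missing baseline values by a simple rule that uses neither arm nor outcome, so that every randomised participant stays in the intention-to-treat analysis. Report the model with the protocol's covariate set as a sensitivity analysis.

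The cost is a few lines of analysis-plan wording, two or three more coefficients, the imputation rule, and a hazard ratio to be read as conditional on more baseline factors. No new data collection is needed for wattage and PANSS, nor for SES or DAI if they were taken at visit 1. Because recruitment is well advanced, the change should be dated and documented as made while the analysing statistician is still blinded.

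### The terms listed for the secondary-endpoint repeated-measures model include no baseline adjustment, so the treatment contrast is in effect a change-score difference: valid, but less precise than the data allow

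*Protocol article*

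**What the plan says.** The section on planned data analyses states the target: "We will analyze changes in neurocognitive performance, psychopathological symptoms, level of functioning, quality of life, cardiovascular risk factors, metabolic parameters, and physical fitness". These domains match the list under study endpoints: "Secondary endpoints include changes in neurocognitive performance, psychopathology, level of functioning, quality of life, cardiovascular risk factors, metabolic parameters, and physical fitness". The model is a mixed model for repeated measurements with "main effects: group, center, sex, participants age, (possibly) duration of illness, time, individual antipsychotic therapy", continued by "and the interaction group × time) and generalized estimation equations (GEE), both between groups and over the course of the study".

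The baseline value of the outcome does not appear among these terms, nor does a baseline × time term or a constraint that the arms share a baseline mean. No other section adds one. CGI severity is mentioned, but only as a possible moderator. Baseline values will exist: under the description of the interventions, "participants complete the diagnostic, clinical, and neurocognition- and performance-related baseline assessments" before training starts, and the study timeline places visit 1 before the intervention.

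**The concern.** For a repeatedly measured continuous outcome, its own baseline value is usually the strongest predictor available. The list goes down to a covariate marked as only possible, yet leaves this one out. A team that follows it as written gets wider confidence intervals than the data require for cognition, symptoms, functioning, quality of life, metabolic risk and fitness. These endpoints also carry a multiplicity correction, so precision matters. At stake is the efficiency of the secondary comparisons, not their validity.

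**Working it through.** **Inputs.** n = 90 per arm (power calculation). An illustrative true difference of 0.33 SD, the meta-analytic effect on global cognition cited in the introduction. Assumptions not found in the documents: a baseline-to-follow-up correlation ρ from 0.3 to 0.8, equal SDs at both times, complete data, one post-baseline visit, and a negligible contribution from the other listed covariates.

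**The plan's own figure.** The article gives no sample size or power for the secondary endpoints. The 90 per arm comes from the primary endpoint, with "we assumed a one-year discontinuation rate of 68% in the control group" and "superiority of 20 percentage points in the one-year discontinuation rate". With unpooled variance, (1.960 + 0.842)² × (0.68×0.32 + 0.48×0.52) / 0.20² = 7.849 × 0.4672 / 0.04 = 91.7, so 92, in line with about 90. (Pooled variance gives 95.) Here it serves only as n.

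**Step 1: which contrast the listed terms estimate.** Let D0 and D1 be the between-arm differences at baseline and at follow-up.
- Change as response: the group contrast is D1 − D0.
- Baseline as first level of time, with free group effect and group × time: the group term fits D0 and group × time fits D1 − D0. With complete data this is the same contrast.

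**Step 2: variances, in units of 2·SD²/n.**
- Change score: 2(1−ρ)
- Baseline-adjusted: 1−ρ²
- Ratio adjusted/change: (1−ρ²) / [2(1−ρ)] = (1+ρ)/2

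| ρ (assumed) | Change score | Adjusted | Ratio | Excess variance of change score | Power at 0.33 SD, change → adjusted |
|---|---|---|---|---|---|
| 0.3 | 1.40 | 0.91 | 0.65 | 54% | 46.5% → 64.1% |
| 0.5 | 1.00 | 0.75 | 0.75 | 33% | 60.0% → 72.4% |
| 0.6 | 0.80 | 0.64 | 0.80 | 25% | 69.7% → 79.0% |
| 0.7 | 0.60 | 0.51 | 0.85 | 18% | 81.5% → 87.3% |
| 0.8 | 0.40 | 0.36 | 0.90 | 11% | 93.8% → 95.8% |

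The excess is 1/ratio − 1. Power is for a single two-sided 5% test. A simulation of 20,000 trials with 90 per arm at ρ = 0.3, 0.5 and 0.7 matched these variances to within about 2%.

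**Step 3: the same loss seen conditionally.** Given a chance baseline difference d, the expected change-score estimate is shifted by −(1−ρ)d; the adjusted estimate is shifted by about zero. The chance SD of d with 90 per arm is √(2/90) = 0.149 SD. A difference of that size shifts the estimate by −0.104 SD at ρ = 0.3, −0.075 at ρ = 0.5 and −0.030 at ρ = 0.8. A difference of 0.2 SD or more in either direction, which occurs by chance in about 18% of trials, shifts it by at least 0.10 SD in size at ρ = 0.5.

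This is not a second harm. 2(1−ρ) = (1−ρ²) + (1−ρ)², and the last term is exactly the variance of the shift, already contained in the change-score standard error.

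**The case against.** The strongest reply is that one parenthesis in a condensed article covers seven domains. It is provisional in places, never says the list is complete, and does not fix the response or the visits that enter; an outcome-specific baseline term could stand in the full plan. That stands as a limit on certainty: the point concerns the terms as listed. It does not remove the point, because the list is specific and leaves out an important term.

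A second reply is that with group, time and group × time, baseline is naturally the first level of time and so is in the model. That is a fair reading, but with a free group effect it gives the change-score contrast of step 1. With missing visits the equality is no longer exact.

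Three stronger readings are tempting, and the documents do not support them.
- A reader might infer that the secondary estimates are biased or the tests invalid. Under randomization the change-score difference is unbiased and the type I error is kept.
- A reader might infer that chance baseline imbalance is left in the estimate, and that precision should be compared with a model that ignores baseline. Both would require raw follow-up values as the response, and the article says it analyzes changes. On that reading imbalance is over-corrected, by (1−ρ)d.
- A reader might count wider intervals and imbalance as two harms. Step 3 shows they are one.

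It would also go too far to say that every outcome has a baseline in every participant: accelerometer measurement, for example, depends on the participant's agreement.

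**Conclusion.** The point holds as one of efficiency. The listed terms lead to a change-score contrast that is valid but less precise than a baseline-adjusted one. The excess variance is 11% at ρ = 0.8 and 54% at ρ = 0.3, so the loss is small where the correlation is high and appreciable where it is moderate. These sizes rest on assumed ρ, equal SDs, complete data and a single post-baseline visit; the direction does not depend on the value of ρ, since adjustment does not lose precision asymptotically. The primary Cox analysis and the sample size are not affected. This is a free improvement, not the correction of an invalid analysis.

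**What to change.** State how baseline enters the secondary-endpoint model, in one of two ways:
- use post-baseline visits only as the response, and add the outcome's baseline value and baseline × time as covariates; or
- keep baseline as a response and constrain both arms to a common baseline mean.

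The cost is about one sentence in the analysis plan, settled before unblinding. No new data are needed.
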